## Abstract

**Introduction:**

The mainstay of treatment for idiopathic sudden sensorineural hearing loss (SSNHL) includes oral steroids, intratympanic steroid injections or a combination of both. The National Institute for Health and Care Excellence, in their recent hearing loss guidelines, highlighted the paucity of evidence assessing the comparative effectiveness of these treatments; and the National Institute for Health Research (NIHR) Health Technology Assessment Programme has since released a commissioned call for a trial to identify the most effective route of administration of steroids as a first-line treatment for idiopathic SSNHL. For such trials to be run effectively, reliable information is needed on patients with SSNHL: where they present, numbers, demographics, treatment pathways, as well as outcomes. This study will collect these data in a nationwide cohort study of patients presenting with SSNHL across 97 National Health Service (NHS) trusts. The study will be delivered through ear, nose and throat (ENT) trainee networks, the NIHR Clinical Research Network (CRN) Audiology Champions and the NIHR CRN. Importantly, this study will also provide a dataset to develop a prognostic model to predict recovery for patients with idiopathic SSNHL. The study objectives are to: (1) map the patient pathway and identify the characteristics of adult patients presenting to NHS ENT and hearing services with SSNHL, (2) develop a prognostic model to predict recovery for patients with idiopathic SSNHL and (3) establish the impact of idiopathic SSNHL on patients’ quality of life (QoL).

**Methods and analysis:**

Study design: national multicentre prospective cohort study across 97 NHS trusts.

Inclusion criteria: adult patients presenting to NHS ENT and hearing services with SSNHL.

Outcomes: change in auditory function; change in QoL score.

Analysis: multivariable prognostic model, using prespecified candidate predictors. Mean change in QoL scores will be calculated from initial presentation to follow-up.

**Ethics and dissemination:**

Health Research Authority and NHS Research Ethics Committee approved the study. Publication will be on behalf of study sites and collaborators.

**Trial registration number:**

ClinicalTrials.gov Registry (NCT04108598).

Strengths and limitations of this studyTaking place across 97 National Health Service trusts, the SeaSHeL Study represents the first nationwide prospective cohort study of adults presenting to ear, nose and throat (ENT) and hearing services with sudden sensorineural hearing loss (SSNHL).It is uniquely delivered by National ENT Trainee Research Network, Student and Foundation Doctors in Otolaryngology, National Institute for Health Research (NIHR) Clinical Research Network (CRN) Audiology Champions and the NIHR CRN.We acknowledge that duration between onset of SSNHL and presentation to ENT services as well as follow-up times and treatment strategies will vary across centres and cases, which may impact measured outcomes; however identifying differences in the patient pathway will form an important study finding.

## Introduction

Each year approximately 20 people per 100 000 experience a sudden hearing loss in one ear that is located in the inner ear.^1^ This is called sudden sensorineural hearing loss (SSNHL), defined as a rapid loss of hearing occurring over 3 days, of 30 dB (decibel) or more, over at least three contiguous sound frequencies.^2^ SSNHL is predominantly unilateral and the degree of hearing loss can range from mild to profound. In 71%–90% of cases, the cause is unknown despite investigation, and these cases are termed idiopathic SSNHL.^3 4^

Idiopathic SSNHL is a serious condition, adversely impacting people’s lives^5^ with research showing associations with emotional distress, depression, difficulties at work and impaired social integration.^6 7^ Its prognosis is poorly understood and may depend on age, comorbidities, degree of hearing loss, audiometric configuration, presence of vertigo, treatment received, time between onset of hearing loss and treatment, and other factors. It is estimated that 32%–65% of cases of idiopathic SSNHL recover spontaneously, although clinical experience suggests that this may be an overestimation, with further research required in this area.^2 8 9^

Current care pathways for patients suffering from SSNHL appear to vary considerably in terms of the type of service patients first present to, their subsequent referral, length of time between onset of symptoms, presentation and start of treatment, the treatment plan as well as follow-up. The mainstay of treatment options for idiopathic SSNHL include oral steroids, intratympanic steroid injections or a combination of both.^5^ The National Institute for Health and Care Excellence, in their recent guidelines on hearing loss (NG98), highlighted the paucity of evidence assessing the comparative effectiveness of these treatments and issued a high priority research recommendation to identify the most effective route of administration of steroids as a first-line treatment for idiopathic SSNHL.^10^ The National Institute for Health Research (NIHR) Health Technology Assessment Programme has since released a commissioned call for a trial to address this question.^11^

For such a trial to be run effectively, reliable information is needed on patients with SSNHL: where they present, numbers, demographics, treatment pathways, as well as outcomes. This study will collect these data in a nationwide prospective cohort study of adult patients presenting with SSNHL across 97 National Health Service (NHS) trusts. The study will be delivered through National ENT Trainee Research Network (INTEGRATE), Student and Foundation Doctors in Otolaryngology (SFO-UK), NIHR Clinical Research Network (CRN) Audiology Champions, and the NIHR CRN. Importantly, this study will not only provide key data to inform trial design and delivery, but also a unique dataset to develop a prognostic model to predict recovery for patients with idiopathic SSNHL.

### Objectives

To map the patient pathway and identify the characteristics of adult patients presenting to NHS ear, nose and throat (ENT) and hearing services with SSNHL.To develop a prognostic model to predict recovery for patients with idiopathic SSNHL.To establish the impact of idiopathic SSNHL on patients’ quality of life (QoL).

## Methods and analysis

### Study design

National multicentre prospective observational cohort study. The study will be reported in accordance with Strengthening the Reporting of Observational Studies in Epidemiology and ‘Transparent Reporting of a multivariable prognostic model for Individual Prognosis or Diagnosis’ reporting guidelines for observational studies.^12^

### Setting

A multicentre study taking place across 97 NHS trusts providing ENT and hearing services.

### Inclusion criteria

Adult patients (man or woman) aged over 16 years of age presenting to NHS ENT and hearing services with a history of sudden hearing loss (within a 72-hour window) that is sensorineural in nature.

There is a decrease in hearing of ≥30 dB affecting at least three consecutive frequencies (between the following specific frequencies: 250 Hz, 500 Hz, 1000 Hz, 2000 Hz, 4000 Hz and 8000 Hz), using a premorbid pure tone audiogram as a baseline reference. Or should a baseline pure tone audiogram not be available, the unaffected ear can be used a baseline reference. Or should both ears be affected by hearing loss, a normative reference (ISO7029)^13^ can be used as the baseline reference.

Willing and able to provide written informed consent.

### Exclusion criteria

Patients with mixed or conductive hearing loss (CHL) in ear(s) with the sudden hearing loss. CHL will be defined as a ‘true’ air-bone gap of 15 dB or more in 3 or more contiguous frequencies, between the following specific frequencies: 500 Hz, 1000 Hz, 2000 Hz and 4000 Hz.

### Sample size and recruitment

The minimum sample size for developing a multivariable prognostic model to predict recovery for patients with idiopathic SSNHL was estimated using the method reported by Riley *et al*.^14^ Assuming a prevalence (ie, full recovery of idiopathic SSNHL) of between 32% and 65%,^2 8 9^ a Nagelkerke’s R-squared of 0.5,^14^ a 0.05 margin of error in estimation of intercept, and a shrinkage factor of ≥0.95, with our prespecified number of predictor parameters of 15, resulted in a minimum sample size of 510 patients. Assuming that 70% of patients with SSNHL are idiopathic cases, this gives a total study minimal sample size of 730 patients.^3 4^

Ninety-seven NHS trusts across the UK have been identified as study sites via INTEGRATE, SFO-UK, NIHR CRN Audiology Champions and the NIHR CRN. An audit carried out in preparation of this study at five NHS trusts, over 6 months, revealed an average presentation rate of one patient with idiopathic SSNHL per trust per month. It appears therefore that our recruitment target over the study duration (32 months) is feasible.

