### Candidate predictors for prognostic model

Age; gender; social class; presence of vestibular symptoms; precipitating illness; pattern of hearing loss; severity of hearing loss; time between onset of symptoms and treatment; treatment(s) received.

Pattern of hearing loss will be defined as: low frequency loss (250 Hz, 500 Hz and 1000 Hz), mid-frequency loss (500 Hz, 1000 Hz and 2000 Hz), high-frequency loss (2000 Hz, 4000 Hz and 8000 Hz) and all frequencies. Severity of hearing loss (on presentation) will be defined as follows: pure tone average (PTA) across six frequencies (250 Hz, 500 Hz, 1000 Hz, 2000 Hz, 4000 Hz and 8000 Hz), classified as: mild (25–40 dB loss), moderate (41–70 dB loss), severe (71–95 dB loss) and profound (>95 dB loss).

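### The 32%–65% used as the rate of full recovery is the Introduction's range for spontaneous recovery; nothing supports it for the 10 dB outcome under usual care, and the sample size is not shown outside it

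*Protocol article*

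**What the plan says.** The protocol article uses one numerical range for two quantities.

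- **Introduction:** "It is estimated that 32%–65% of cases of idiopathic SSNHL recover spontaneously". The sentence continues: "although clinical experience suggests that this may be an overestimation, with further research required in this area". The degree of recovery is not stated.
- **Sample size and recruitment:** "Assuming a prevalence (ie, full recovery of idiopathic SSNHL) of between 32% and 65" per cent, with the same three references and without the caution. The other inputs are "a Nagelkerke’s R-squared of 0.5", "a 0.05 margin of error in estimation of intercept", a shrinkage factor of at least 0.95 and 15 predictor parameters. The stated result is 510 idiopathic patients, or 730 in total if 70% of cases are idiopathic.
- **Primary outcome:** full recovery means a final pure tone average in the affected ear within 10 dB of the reference, measured 6 to 16 weeks after onset. Everything else is a non-event. Under Secondary outcomes, a gain of 30 dB or more that misses the 10 dB target is marked recovery, not complete recovery.
- **Candidate predictors:** the list ends with "time between onset of symptoms and treatment; treatment(s) received", so treated patients are in the cohort. The Introduction says of usual care: "The mainstay of treatment options for idiopathic SSNHL include oral steroids, intratympanic steroid injections or a combination of both".

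**The concern.** The event rate enters the calculation directly. With Nagelkerke R-squared held at 0.5, the corresponding Cox–Snell R-squared is largest at a rate of 50% and shrinks as the rate moves away in either direction. A smaller Cox–Snell value means more patients are needed to hold shrinkage at 0.95. A minimum worked out only over 32%–65% therefore gives no assurance if full recovery, as this study defines it, falls outside that range.

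The protocol gives two reasons to doubt the fit. It says itself that the range may be too high. It also moves from spontaneous recovery of unstated degree to a defined 10 dB outcome in patients who may be treated, with no argument connecting the two. The prognostic model is one of the three study objectives, and this minimum exists to limit its overfitting.

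**Working it through.** **Inputs (Sample size and recruitment):** P = 15 parameters; Nagelkerke R² = 0.5; target shrinkage S = 0.95; intercept margin 0.05; event rate φ from 0.32 to 0.65; idiopathic share 0.70. Rates outside 32%–65% are assumptions, because the article gives no full-recovery rate on its own definition.

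**Formulas (Riley criteria, binary outcome):**

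- Maximum Cox–Snell R² = 1 − exp{2[φ ln φ + (1−φ) ln(1−φ)]}
- Cox–Snell R² = 0.5 × maximum
- Shrinkage criterion: n = P / [(S−1) ln(1 − R²cs/S)]
- Intercept criterion: n = (1.96/0.05)² φ(1−φ)

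**The plan's own figure.** At φ = 0.32 the maximum is 0.7146 and R²cs is 0.3573. Then ln(1 − 0.3573/0.95) = −0.4717, and n = 15/(0.05 × 0.4717) = 636. The same steps give 598 at 50% and 624 at 65%. The intercept criterion gives 335, 385 and 350. The criterion limiting optimism in R² to 0.05 gives 331, 311 and 324. The shrinkage criterion therefore governs, and the range is 598–636. The lowest value at any rate is 598, so 510 is not reproduced. The step 510/0.70 = 729 does agree with the stated 730.

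**Effect of the event rate, other inputs unchanged.** The last column solves the shrinkage criterion for S at n = 510.

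| Full-recovery rate | R²cs | Minimum idiopathic n | Total (n/0.70) | Expected shrinkage at n = 510 |
|---|---|---|---|---|
| 50% (within stated range) | 0.3750 | 598 | 855 | 0.942 |
| 65% (stated upper end) | 0.3630 | 624 | 892 | 0.940 |
| 32% (stated lower end) | 0.3573 | 636 | 909 | 0.939 |
| 25% (assumed) | 0.3376 | 684 | 978 | 0.934 |
| 20% or 80% (assumed) | 0.3162 | 742 | 1,060 | 0.929 |
| 15% (assumed) | 0.2853 | 840 | 1,200 | 0.921 |

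**Part due to the event rate alone.** Against 636 at 32%, the minimum rises by 48 (8%) at 25%, 106 (17%) at 20% or 80%, and 204 (32%) at 15%. At n = 510 shrinkage is already 0.939 at 32%. Moving to 25%, 20% or 15% takes it to 0.934, 0.929 or 0.921. The step from 0.95 to 0.939 comes from 510 being too small for the stated inputs, not from the choice of range.

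**Feasibility.** 97 trusts × 32 months × 1 patient per month = 3,104 idiopathic presentations at the audit rate.

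**The case against.** The best defence is that the cited sources may have counted complete recovery, so that the sample-size section is the exact statement and the Introduction the loose one. The documents cannot settle this. It does mean that a reader should not infer that the range covers recovery of any degree, because the Introduction leaves the degree open.

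Nor should a reader infer that 32%–65% is the wrong figure, or that it is too high for this cohort. The Introduction's caution concerns spontaneous recovery. A strict 10 dB criterion could lower the rate and treatment could raise it, and no document gives the net effect. Both sections concern idiopathic cases. The difference is natural course against usual care, not two different diseases or patient groups.

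A reader might also take the borrowed range to be the reason for 510. It is not, since no event rate yields that number.

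Finally, 510 is stated as a minimum, the audit rate points to far more presentations, and the Statistical analysis section plans bootstrap validation with a shrinkage factor applied to the coefficients. These points limit the consequence. However, measuring and correcting optimism afterwards does not replace an adequate size, and presentations are not followed-up patients.

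What remains is that the article uses a range it doubts itself, under a different label, without justification and without showing the result outside it.

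**Conclusion.** The concern holds as a point about an unsupported input. The mismatch of label, and the loss of the caution between the two sections, are plain from the text. The size of the effect is conditional. It is nil if full recovery lies within 32%–65%, where a correctly computed minimum is at most 636. It is modest at 25% (684), and material at 20% or 80% (742) and at 15% (840). These figures assume 15 parameters, a Nagelkerke R-squared that stays at 0.5 whatever the event rate, and a shrinkage target of 0.95.

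The failure of 510 to follow from the stated inputs is a separate and larger defect. Correcting it would bring the minimum to about 636, which would still be too small if full recovery is rarer than 32% or, by symmetry, commoner than 68%.

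**What to change.** 1. Reconcile the Introduction with the sample-size section. Either label 32%–65% as spontaneous recovery in both places, or show from the cited sources that it applies to recovery within 10 dB under usual care.
2. State the minimum, and the shrinkage expected at the planned number, over a range widened on both sides, for example 15%–80%, labelled as an assumption.
3. Before recruitment closes, recompute the minimum from the pooled full-recovery proportion in idiopathic patients, without looking at any predictor. If the planned number is kept, report the shrinkage it delivers.

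The work amounts to a revised paragraph and one pooled count from data the study already collects. The price is a less favourable stated minimum or shrinkage. Numbers are unlikely to be the obstacle, since even 840 is about 27% of the roughly 3,100 idiopathic presentations implied by the audit rate (840/3,104). Those presentations are not guaranteed to become complete cases, so the revised text should not treat them as such.

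### At the protocol's own inputs, 510 idiopathic patients give an expected shrinkage factor of about 0.94, not at least 0.95, and less if R-squared is below 0.5

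*Protocol article*

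**What the plan says.** Under Sample size and recruitment, the protocol article applies a published minimum-sample-size method for prediction models (reference 14). It lists these inputs:

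- "Assuming a prevalence (ie, full recovery of idiopathic SSNHL) of between 32% and 65"%, citing references 2, 8 and 9;
- "a Nagelkerke’s R-squared of 0.5,^14^ a 0.05 margin of error in estimation of intercept, and a shrinkage factor of ≥0.95", citing reference 14 again for the R-squared;
- "with our prespecified number of predictor parameters of 15".

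The result is 510 idiopathic patients. Dividing by an assumed 70% idiopathic share (references 3 and 4) gives 730 in total. The Introduction says of the condition: "Its prognosis is poorly understood and may depend on age, comorbidities, degree of hearing loss, audiometric configuration, presence of vertigo". The Statistical analysis section plans bootstrap internal validation, with a shrinkage factor then applied to the regression coefficients.

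**The concern.** Two things stand out. First, 510 looks too small for a 0.95 shrinkage target with 15 parameters, even at an R-squared as high as 0.5. Second, the R-squared is the most influential input, and a higher value always gives a smaller study. The prevalence and the idiopathic share each have their own sources, and prevalence is given as a range. The R-squared is a single value, cited only to the reference used for the method.

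The shrinkage target is the design's stated protection against overfitting. If 510 patients do not meet it, a reader who relies on the paragraph will expect less optimism in the model than the design allows for.

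**Working it through.** **Inputs from the protocol article:** P = 15 parameters; recovery proportion p = 0.32 to 0.65 (0.50 added as an interior point, where the requirement is smallest); Nagelkerke R-squared 0.5; target shrinkage S = 0.95; margin of error 0.05; stated N = 510.

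**Formulas** (the usual binary-outcome criteria, taken to be those of the cited method, which is not itself available here):

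- Maximum Cox-Snell R-squared = 1 − exp{2[p ln p + (1−p) ln(1−p)]}
- R²cs = Nagelkerke R-squared × that maximum
- Shrinkage: n = P / [(S − 1) ln(1 − R²cs/S)]
- Overall risk: n = (1.96/0.05)² p(1−p)
- Optimism in Nagelkerke R-squared of at most 0.05: the shrinkage formula with S = 0.5/(0.5 + 0.05) = 0.909

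**Step 1: the plan's own figure.** At p = 0.50 the maximum is 0.750, so R²cs = 0.375, ln(1 − 0.375/0.95) = −0.502, and n = 15/(0.05 × 0.502), about 598.

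| p | Max R²cs | R²cs | n, shrinkage 0.95 | n, optimism | n, overall risk | S at n = 510 |
|---|---|---|---|---|---|---|
| 0.32 | 0.715 | 0.357 | 636 | 331 | 335 | 0.939 |
| 0.50 | 0.750 | 0.375 | 598 | 311 | 385 | 0.942 |
| 0.65 | 0.726 | 0.363 | 624 | 324 | 350 | 0.940 |

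The stated 510 is not reproduced. The shrinkage criterion dominates: the other two need at most 385. At the 70% idiopathic share, 598 to 636 becomes 855 to 909 in total. The final step does reproduce: 510/0.70 = 729, reported as 730.

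**Step 2: other readings.** A target of 0.90 needs 279 to 297. Taking 0.5 as a Cox-Snell value needs 402. A likelihood-ratio version of the shrinkage formula needs 639 to 679. A figure near 510 appears only if a stated input is changed, for example to 12 parameters at p = 0.32 (509), to S = 0.94 at p = 0.65 (513), or to a Nagelkerke R-squared of about 0.56 to 0.59.

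**Step 3: sensitivity to R-squared.** The values below 0.50 are assumptions of this review; the document gives no alternative. P = 15 and p = 0.32 to 0.65 throughout.

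| Nagelkerke R-squared | S at n = 510 | n for S = 0.95 |
|---|---|---|
| 0.50 (protocol) | 0.939–0.942 | 598–636 |
| 0.40 | 0.921–0.925 | 791–839 |
| 0.30 | 0.893–0.898 | 1,110–1,174 |
| 0.20 | 0.842–0.849 | 1,746–1,841 |
| 0.15 | 0.797–0.805 | 2,381–2,506 |

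**Step 4: availability of patients.** The preparatory audit found one idiopathic patient per trust per month. Over 97 trusts and 32 months that is 97 × 32 = 3,104 presentations, before losses to non-recruitment and follow-up.

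**The case against.** The 0.95 is a target listed among the assumptions, so the paragraph makes no unconditional promise. That is right, and it limits the point: the fault is that the target is not met under the conditions given.

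A reader might infer that the Introduction's remark on prognosis contradicts an R-squared of 0.5. It does not. The remark describes present knowledge and gives no figure for explainable variation. Severity at presentation is a candidate predictor measured over the same six frequencies as the outcome, so a strong predictor is plausible.

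A reader might also infer that the model will be overfitted by 10% to 20%. That holds only at R-squared values of about 0.15 to 0.30, which no document supports. At 0.40 to 0.45 the figure is 7% to 8%, and at the protocol's own 0.5 it is about 6%.

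Whether reference 14 justifies 0.5 cannot be checked here. A condensed article may also leave that justification, and any sensitivity range, to a fuller document, so their absence alone is no fault.

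The planned bootstrap shrinkage adjusts the coefficients afterwards and so reduces the harm. It does not make 510 meet the design target. The paragraph already calls 510 and 730 minimum figures, so asking for them to be labelled a floor would add little.

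**Conclusion.** The point stands in a limited form. With every input as printed, 510 idiopathic patients give an expected shrinkage of 0.939 to 0.942, and the target of 0.95 needs 598 to 636. This part needs no outside value for R-squared; it rests only on the shrinkage criterion above being the one the cited method uses.

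The shortfall at R-squared 0.5 is small, about one percentage point of shrinkage. It grows if the predictors explain less: about 0.92 at 0.40, 0.89 to 0.90 at 0.30 and 0.80 at 0.15. These show how fragile the figure is and do not predict the model's performance. The documents do not show that 0.5 is wrong.

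**What to change.** In Sample size and recruitment, replace the shrinkage factor of at least 0.95 with what 510 patients deliver: about 0.94 at a Nagelkerke R-squared of 0.5, for recovery of 32% to 65%. Beside it, give the expected shrinkage at lower R-squared values (for example 0.40, 0.30 and 0.15), labelled as a sensitivity range. If 510 was calculated from inputs other than those printed, state those inputs.

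The cost is a reworded paragraph and a less favourable stated figure. No extra sites or longer recruitment are needed.

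### The stated minimum of 510 idiopathic patients does not follow from the plan's own inputs, which give 598 to 636; at 510 the expected shrinkage is about 0.94, not 0.95 or better.

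*Protocol article*

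**What the plan says.** The protocol article, Sample size and recruitment, says that the minimum size for the prognostic model "was estimated using the method reported by Riley" and colleagues. The inputs given there are:

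- a prevalence of full recovery between 32% and 65%;
- "a Nagelkerke’s R-squared of 0.5";
- "a 0.05 margin of error in estimation of intercept";
- "a shrinkage factor of ≥0.95";
- 15 predictor parameters, a count that the Statistical analysis section repeats.

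The result is given as follows: "with our prespecified number of predictor parameters of 15, resulted in a minimum sample size of 510 patients". The section then assumes that 70% of cases are idiopathic and concludes that "this gives a total study minimal sample size of 730 patients". Both figures are called minimums. The same section reports an audit rate of one idiopathic patient per trust per month, and uses it to argue that recruitment across 97 trusts over 32 months is feasible.

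**The concern.** All the inputs that decide the answer are printed beside the result, so the calculation can be repeated without any other document. It does not return 510. The prognostic model is one of three study objectives and the only basis given for the sample size. A reader will take 510 as the number at which a 15-parameter model meets the shrinkage criterion of 0.95. If it is not, a model built at the declared minimum would be somewhat more overfitted than the plan says. The total of 730 carries the same error.

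**Working it through.** **Step 1. The plan's own figures.** The second step reproduces: 510/0.70 = 728.6, stated as 730. The first step, from the inputs to 510, does not, as shown below.

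**Step 2. From Nagelkerke to Cox-Snell R-squared.** For recovery prevalence φ, the largest possible Cox-Snell value is max R²cs = 1 − [φ^φ (1−φ)^(1−φ)]². The anticipated value is R²cs = 0.5 × max R²cs.

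**Step 3. The criteria.** With P = 15 parameters and target shrinkage S = 0.95:

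- Shrinkage: n = P / [(S − 1) ln(1 − R²cs/S)].
- Intercept: n = (1.96/0.05)² φ(1 − φ), taking the 0.05 margin at 95% confidence.
- Optimism in R-squared: the shrinkage formula with S = R²cs/(R²cs + 0.05 max R²cs) = 0.909. The article does not list this 0.05 tolerance. It is an assumption here, and this criterion does not govern.

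The method takes the largest of these.

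| Recovery φ | max R²cs | R²cs | Shrinkage n | Intercept n | Optimism n | Required n | Total at 70% idiopathic |
|---|---|---|---|---|---|---|---|
| 0.32 | 0.7146 | 0.3573 | 635.9 | 334.4 | 330.5 | 636 | about 909 |
| 0.50 | 0.7500 | 0.3750 | 597.5 | 384.2 | 310.2 | 598 | about 854 |
| 0.65 | 0.7261 | 0.3630 | 623.1 | 349.6 | 323.7 | 624 | about 891 |

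Worked line at 32%: 0.3573/0.95 = 0.3761; ln(1 − 0.3761) = −0.4718; 15/(0.05 × 0.4718) = 636.

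The shrinkage criterion governs throughout. Its lowest value in the stated range is at 50% and its highest at 32%, so the required size is 598 to 636.

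**Step 4. The gap.** At 50%: 598 − 510 = 88, and 88/598 = 15%. At 32%: 636 − 510 = 126, and 126/636 = 20%. In total, the gap is 854 − 730 = 124 to 909 − 730 = 179.

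**Step 5. What 510 delivers.** Solving the shrinkage formula for S at n = 510 and P = 15 gives 0.939 at 32%, 0.942 at 50% and 0.940 at 65%. All are below 0.95.

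**Step 6. Other readings, all with 15 parameters.**

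- Taking 0.5 as the Cox-Snell value: 402.
- Not dividing R²cs by S: 639 to 679.
- Target shrinkage of 0.90: 279 to 297 for that criterion, so the intercept criterion would then govern at 335 to 385.
- A mean absolute prediction error criterion at 0.05, which the article does not mention: 692 or more.

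None gives 510. Reaching 510 means changing a stated input, for example Nagelkerke R-squared to about 0.56 to 0.59, or S to about 0.94.

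**The case against.** The strongest reply is that the practical consequence is small, and most of that reply stands. Expected shrinkage at 510 is only about one percentage point below the target. The Statistical analysis section also plans bootstrap validation with a shrinkage factor applied to the coefficients, so extra optimism would be estimated and adjusted for. That softens the consequence, but it does not make the printed minimum satisfy the criterion from which it is said to come.

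Three stronger readings are tempting, and the documents do not support them.

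- *That the study will stop at 730 and so end up too small.* The article does use the phrase recruitment target, but it calls both figures minimums, gives no rule for stopping at them, and sets a calendar end date. The audit rate implies 97 × 32 = 3,104 idiopathic presentations, and 636 is about 20% of that. Actual capture may fall below the audit rate, but nothing in the document makes 510 a ceiling.
- *That recovery below 32% should be assumed, so the need exceeds 636.* The Introduction does say of the 32% to 65% range, "although clinical experience suggests that this may be an overestimation". That remark concerns spontaneous recovery, whereas treatment received is a candidate predictor in this cohort. No lower rate is given on which to calculate.
- *That 510 came from a 12-parameter calculation.* Twelve parameters at 32% do give 508.8, but the same count gives 478 at 50% and 498 at 65%. A higher R-squared with 15 parameters also reaches 510. The article does not say where the number came from, and the point does not depend on it.

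It is also fair to say that the 20% shortfall applies only at the 32% end. The article gives a range without saying which value governs, so the gap is best stated as 15% to 20%.

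**Conclusion.** The point holds as an arithmetic error in the stated floor. On the plan's own inputs the minimum is 598 to 636 idiopathic patients (about 854 to 909 in total), against the stated 510 and 730. No prevalence between 32% and 65% yields 510, and at that size a 15-parameter model has an expected shrinkage of about 0.94.

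This rests on the standard form of the Riley criteria for a binary outcome, on 15 parameters as stated twice, and on taking Nagelkerke R-squared 0.5 at face value. It does not show that the final dataset will be too small or that the model will be unreliable. The sentence should be corrected because the design cites it, but the consequence is modest.

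**What to change.** Do one of the following in Sample size and recruitment:

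- Restate the minimum as 636 idiopathic patients and 909 in total, and say that this is the worst case over the stated recovery range (at 32%).
- Keep 510 and 730, and state that with 15 parameters they support an expected shrinkage of about 0.94 in place of 0.95 or better.

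Either is a one-sentence change with no effect on procedures or analysis. The first raises the stated floor by 126 idiopathic patients (179 in total), which remains well within the roughly 3,100 idiopathic presentations implied by the audit rate. The second costs only a slightly less favourable design statement.
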